#### Primary endpoint analysis

2.6.1

To assess the primary endpoint of the study, Kaplan–Meier survival curves will be constructed to compare the time to first hospitalization between groups. Group differences will be evaluated using the log-rank test. Subsequently, a Cox proportional hazards regression analysis model will be performed to examine the association between the variable “Device Use (Yes vs. No)” and the reduction in hospital admissions. The model will be adjusted for all statistically significant covariates identified through ANOVA between the two groups. To mitigate selection bias resulting from the non-randomized design, propensity score methods will be applied. The propensity score will be estimated using baseline variables including age, sex, LVEF phenotype, NYHA class, major comorbidities (hypertension, atrial fibrillation, diabetes mellitus, COPD/OSA, obesity), prior HF hospitalizations, baseline biomarkers (BNP/NT-proBNP, renal function, electrolytes), and key echocardiographic indices (LVEF, LV volumes). A 1:1 nearest-neighbour matching approach without replacement will be used. Covariate balance between groups will be evaluated using standardized mean differences (SMD), with values <0.10 indicating adequate balance. Results will be expressed as hazard ratios (HR) with corresponding 95% confidence intervals (CI).

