#### Secondary endpoint analysis

2.6.2

Continuous variables will be presented as mean ± standard deviation (SD) for normally distributed data and as median and interquartile range (IQR) for non-normally distributed data. Categorical variables will be expressed as frequencies and percentages. The normality of distribution will be tested using the Shapiro–Wilk test. For normally distributed continuous variables, comparisons will be made using the paired t-test or one-way repeated measures ANOVA, depending on the situation. For non-normally distributed data, the Wilcoxon Signed-Rank test will be applied. Categorical variables will be compared using the Pearson chi-square test. Given the intrinsic differences in echocardiographic and clinical trajectories between HFrEF and HFpEF patients, all secondary endpoints (including echocardiographic parameters, biomarkers, and functional indices) will also undergo stratified analyses by LVEF phenotype. This approach is intended to avoid the dilution of clinically meaningful changes in subgroups with limited baseline variability, particularly among HFpEF patients. Subgroup analyses based on LVEF phenotype (HFrEF, HFmrEF, HFpEF) will be performed as exploratory analyses. The study is not powered to detect statistically significant differences between these subgroups; therefore, these analyses are intended to be descriptive and hypothesis-generating. To mitigate potential confounding when comparing phenotypes, LVEF category will be included as a covariate in multivariable models, and propensity score techniques will be applied when appropriate. Because echocardiographic parameters show markedly different baseline ranges and variability in HFrEF and HFpEF, echocardiographic secondary outcomes will also be interpreted within each LVEF phenotype. This approach is intended to avoid the dilution of true within-group changes in HFpEF patients, in whom structural parameters often fall within or near the normal range. A two-sided *p*-value < 0.05 will be considered statistically significant for all final analyses.

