#### Handling of missing data and dropouts

2.6.4

Missing data and incomplete follow-up will be handled according to established recommendations for observational cohort studies. For clinical, biochemical, and echocardiographic variables, the pattern and mechanism of missingness will be evaluated. When data are missing at random (MAR), multiple imputation using chained equations (MICE) will be applied to reduce bias and preserve statistical power. In case of non-random missingness, sensitivity analyses will be performed using complete-case analysis and worst-case/best-case scenarios. For time-to-event analyses, dropouts will be treated as censored observations at the last available follow-up. Device adherence will be quantified as the percentage of monitoring days with valid wearable data; predefined thresholds for minimum acceptable adherence will be applied in sensitivity analyses. Per-protocol and intention-to-monitor analyses will be conducted to assess the robustness of the findings with respect to missing data and incomplete device use.

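### The stated test of group differences on the primary endpoint is a log-rank with no adjustment stated, in self-selected groups, and the plan does not say which result decides

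*Protocol article*

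**What the plan says.** Section 2.6.1 (Primary endpoint analysis) describes three group comparisons for time to first hospitalization.

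- Kaplan-Meier curves with a log-rank test, which comes first: "Group differences will be evaluated using the log-rank test. Subsequently, a Cox proportional hazards regression analysis model will be performed". The log-rank is the only step said to evaluate group differences, and no adjustment or matching is mentioned for it.
- A Cox model for device use, fitted afterwards: "The model will be adjusted for all statistically significant covariates identified through ANOVA between the two groups".
- Propensity scores: "To mitigate selection bias resulting from the non-randomized design, propensity score methods will be applied". The section lists the baseline variables for the score and adds: "A 1:1 nearest-neighbour matching approach without replacement will be used". Balance is judged by standardized mean differences (SMD) below 0.10. No caliper is stated.

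The section ends by saying that results will be given as hazard ratios with 95% confidence intervals, without saying which hazard ratio.

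Section 2.2 forms the groups by whether patients accept the wearable. Section 2.1 says multivariable regression, propensity matching and stratified analyses will be used to limit selection bias, and does not rank them.

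Two further sentences bear on the point. Section 2.6.2 says "A two-sided *p*-value < 0.05 will be considered statistically significant for all final analyses". Section 2.6.4 says "Per-protocol and intention-to-monitor analyses will be conducted to assess the robustness of the findings".

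**The concern.** Patients who agree to continuous monitoring are likely to differ in risk from those who decline. The Limitations section itself expects older or less digitally literate patients to be underrepresented in the device group. If older patients are at higher risk (an assumption, though a mild one), an unadjusted comparison favours the device even when the device does nothing.

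The protocol recognises this in section 2.1, yet the one step it describes as testing group differences carries no stated adjustment. The adjusted and matched analyses come after it with no order of authority. They use different covariate sets and possibly different patients, so they can disagree with the log-rank and with each other. A reader of the final report could not tell from this document which result was meant to settle the question.

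**Working it through.** **Reading the text.** Section 2.6.1 leaves three things open: whether the log-rank and Cox analyses use the full or the matched cohort, which of the two hazard ratios is the result, and whether the log-rank is a test or a description. The documents give no false-positive rate to reproduce beyond the nominal two-sided 0.05. The sample-size figure plays no part in this point.

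**Size of the problem under no device effect.** The documents give 300 patients, six months, two-sided 0.05, log-rank, Cox with significance-selected covariates, and 1:1 nearest-neighbour matching without replacement. Acceptance rate, event risk and strength of self-selection are not given and are assumed. All confounders are measured, which is the favourable case.

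*Simulation A.* 30% six-month event risk; 12 baseline covariates, four of them prognostic (HR 0.78 per SD) and related to acceptance; 4,000 trials per row. Rejection rates in %:

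| Acceptance | SMD on the four | Crude | Selected-covariate Cox | 1:1 match | Any of three | Conflicting verdicts |
|---|---|---|---|---|---|---|
| 50% | 0 | 4.1 | 4.0 | 3.8 | 5.4 | 2.7 |
| 50% | 0.15 | 9.9 | 5.7 | 7.0 | 10.9 | 6.6 |
| 50% | 0.24 | 19.6 | 5.8 | 13.5 | 20.8 | 16.4 |
| 35% | 0 | 5.1 | 4.9 | 4.4 | 7.6 | 5.6 |
| 35% | 0.15 | 9.4 | 6.0 | 4.4 | 11.7 | 9.6 |
| 35% | 0.24 | 16.1 | 6.0 | 4.8 | 18.3 | 15.9 |

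*Simulation B.* About 1:1 acceptance; 35% risk; 10% drop-out censoring; two risk factors (log HR 0.4 per SD each) drive acceptance with log-odds 0, 0.25 or 0.5 per SD; 1,000 trials each. Rejection rates in %:

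| Self-selection | Crude | Selected-covariate Cox | 1:1 match, no caliper | Any of three |
|---|---|---|---|---|
| None | 4.1 | 3.7 | 3.7 | 4.9 |
| Mild | 13.9 | 6.0 | 9.5 | 15.8 |
| Moderate | 34.8 | 6.8 | 23.1 | 38.8 |

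Of the crude rejections, 13.5 of 13.9 points (mild) and all 34.8 (moderate) favoured the device.

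*Simulation C.* A further run gave crude rejection of 8-12% (mild) and 15-19% (moderate), and any of three 10-13% and 17-21%. The match without a caliper rejected about 14% at 50% acceptance and moderate selection. Caliper matching, overlap weighting, and a Cox model with the pre-listed covariates each stayed near 5-6%.

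**What drives it.** In simulation A, allowing any of three instead of the crude test alone adds 10.9 - 9.9 = 1.0 and 20.8 - 19.6 = 1.2 points at 50% acceptance, and 11.7 - 9.4 = 2.3 and 18.3 - 16.1 = 2.2 points at 35%. For comparison, confounding at SMD 0.24 raises the crude test itself by 19.6 - 4.1 = 15.5 points at 50% acceptance. Multiplicity is minor.

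**Why the match leaks.** Near 50% acceptance the two groups are about the same size. Matching every patient in the smaller group without replacement and without a caliper keeps almost the whole cohort, and with it most of the imbalance. At 35% acceptance there is a larger pool to choose from, and the match held at 4.4-4.8%.

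**The case against.** The strongest reply is that the protocol plainly means to adjust. Sections 2.1 and 5 rely on adjustment as the safeguard, and a log-rank yields no hazard ratio, so reporting hazard ratios points to a Cox result with Kaplan-Meier and log-rank as a customary first step. A single matched pipeline is also a permissible reading. This part stands: the text permits an adjusted result as primary. But it does not fix one, and at least two hazard ratios qualify.

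A reader might infer more than the text supports:

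- *That a significant log-rank counts as a positive trial even if both adjusted hazard ratios are null.* No section gives a success rule. The p < 0.05 sentence sets a level and sits in the secondary-endpoint section.
- *That there are five competing tests.* Section 2.6.4 already presents per-protocol and intention-to-monitor as robustness analyses. Only the main analysis set is unnamed.
- *That testing several times breaks the 5% level.* Without confounding, any of three gave 4.9-7.6%.

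It can also be said that ranking analyses belongs in an analysis plan that is not shown. That would answer a silent protocol. This one specifies the primary analysis down to the matching algorithm and balance threshold, and the test it states sits badly with its own reason for adjusting.

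Finally, the error rates rest on assumed confounding, and simulations A and B did not apply the SMD < 0.10 check. That check could flag a poor match, but the article does not say what would follow, and it does nothing for the unmatched log-rank.

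**Conclusion.** The point holds in a limited form. The primary analysis tests group differences with a log-rank for which no adjustment or matching is stated, in groups formed by patient choice, and does not say whether that test, the Cox hazard ratio or the matched hazard ratio decides, or in which cohort. The crude test is left able to carry the conclusion; the document does not say that it will.

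Under assumed mild to moderate self-selection on measured risk factors, the crude test's false-positive rate is roughly 8-20%, that is 8/5 = 1.6 to 20/5 = 4 times nominal, nearly all false benefit. It reached 34.8% under the stronger confounding of simulation B. With no confounding there is little harm. No document figure fixes the true degree of self-selection, and unmeasured differences could move the result in ways that none of these analyses addresses.

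**What to change.** In section 2.6.1, before outcome data are analysed:

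1. Name one confounding-adjusted hazard ratio as the decision result: device-accepting versus declining patients, intention-to-monitor population, two-sided 0.05, with 95% CI. Use the baseline variables already listed for the propensity score, by one of these methods: overlap weighting with robust standard errors, matching with a stated caliper, or a Cox model with that fixed covariate list. They answer slightly different questions, so the choice must be made in advance.
2. Do not name the 1:1 match as now written as the decision result, since it states no caliper.
3. Call the unadjusted Kaplan-Meier curves and log-rank test descriptive, or replace them with weighted or matched versions.
4. Label the remaining Cox or matched model as a sensitivity analysis, and word the p < 0.05 sentence in section 2.6.2 to fit.

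The change is to wording only, with no new data or patients. The price is that a significant crude log-rank can no longer be reported as the primary result, and a caliper or weighting slightly reduces the effective sample.

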### Study design and population

2.1

The SMART-CARE study is a multicenter, prospective, observational cohort trial, designed to evaluate the clinical utility of artificial intelligence (AI)-enabled remote monitoring in patients with CHF. A prospective, non-randomized observational design was chosen for both ethical and pragmatic reasons. Allocation to the intervention group required patients' explicit willingness to use the wearable device and to undergo continuous monitoring, making randomization unfeasible. To minimize potential selection bias, statistical adjustment methods (multivariable regression, propensity score matching, and stratified analyses by age, sex, New York Heart Association class - NYHA, Left Ventricular Ejection Fraction - LVEF phenotype, and comorbidities) will be applied. The trial will be conducted across three tertiary care centers in Italy: AOU “San Giovanni di Dio Ruggi d'Aragona”, IRCCS Neurolesi “Bonino Pulejo”, and IRCCS Fondazione Casa Sollievo della Sofferenza. The study will enroll 300 adult patients (≥18 years) with a confirmed diagnosis of CHF, including Heart Failure with reduced Ejection Fraction (HFrEF), Heart Failure with mildly reduced Ejection Fraction (HFmrEF), or Heart Failure with preserved Ejection Fraction (HFpEF) for at least six months, who are clinically stable and on optimized medical therapy for at least one month prior to enrolment (Figure 1).

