#### Sample size calculation

2.6.3

Based on the primary objective of the study, a sample size calculation was performed using G*Power software. The estimation assumes a 20% relative reduction in the rate of hospital admissions (including emergency department visits and hospitalizations) in the intervention group compared to the control group. Using a two-sided alpha of 0.05 and a statistical power (1–*β*) of 85%, the required sample size was calculated to be 186 participants. To account for a potential 10% dropout rate, the total planned enrollment is set at 205 patients with chronic HF. However, the study team elected to enroll 300 patients to further strengthen the statistical robustness of the analysis. This larger planned sample provides several advantages:
it compensates for potential attrition, incomplete adherence, or missing data;it increases the precision of effect estimates in a clinically heterogeneous HF population;it enhances the stability of exploratory subgroup analyses across LVEF phenotypes (HFrEF, HFmrEF, HFpEF);it improves the reliability and generalizability of machine-learning models derived from multimodal wearable data.Thus, while 205 participants represent the minimum requirement based on power analysis, the planned enrollment of 300 patients ensures greater analytical robustness and supports the broader aims of the SMART-CARE project.

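### Cox covariates are chosen by ANOVA significance between groups, a rule that tends to miss moderate confounders (SMD below about 0.23), and the plan does not say whether this model or the matched analysis gives the primary hazard ratio

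*Protocol article*

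**What the plan says.** **Allocation.** The Protocol article, Study design and population, explains that "Allocation to the intervention group required patients' explicit willingness to use the wearable device" and that randomization was therefore judged unfeasible. It promises multivariable regression, propensity score matching and stratified analyses against selection bias.

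**Primary analysis.** Primary endpoint analysis starts with Kaplan–Meier curves for time to first hospitalization, for which "Group differences will be evaluated using the log-rank test". A Cox model for device use follows, with this covariate rule: "The model will be adjusted for all statistically significant covariates identified through ANOVA between the two groups".

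**Propensity score.** The next sentences of that section add propensity score methods with a named baseline list: age, sex, LVEF phenotype, NYHA class, five comorbidity items, prior HF hospitalizations, biomarkers and echocardiographic indices. Matching is 1:1 nearest-neighbour without replacement, and an SMD below 0.10 counts as adequate balance. The section does not say whether the screened Cox model or the matched analysis yields the primary hazard ratio, or whether the ANOVA screen is run before or after matching.

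**Level and size.** Secondary endpoint analysis gives a two-sided 0.05 threshold that "will be considered statistically significant for all final analyses"; no separate level is given for the screen. On size, Sample size calculation says: "However, the study team elected to enroll 300 patients to further strengthen the statistical robustness of the analysis". The minimum there is 205.

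**The concern.** Confounding is roughly the product of two things: how far a covariate differs between the groups and how strongly it predicts admission. A significance test of the group difference looks at the first only, and through a p-value that depends on sample size. A strong predictor with a moderate imbalance can be left out, while an imbalanced variable unrelated to admission is put in. Chance decides which model is fitted, and the reported confidence interval takes no account of that.

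The rule also applies a different standard of imbalance from the SMD criterion in the same section. At stake is the primary hazard ratio: if the screened model supplies it, the estimate keeps confounding that covariates already collected could remove. The Limitations section expects older patients and those less at ease with digital tools to be scarcer in the device group, which makes a bias towards the device plausible.

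**Working it through.** **Inputs from the plan.** 300 patients; selection by significance of a between-group ANOVA; two-sided 0.05; SMD limit 0.10. The plan gives no figure for how often the screen misses a confounder, so there is none to reproduce.

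**Assumptions.** Split 150:150, with 200:100 and 225:75 as the range, since no ratio is stated. The 0.05 level is taken to apply to the screen. Imbalances, covariate strengths and event risk are not in the documents and are varied below.

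**1. Where the two rules collide.** For two groups, ANOVA is a t test with t = SMD × √(n₁n₂/(n₁+n₂)). At 150:150 the multiplier is √75 = 8.660 and the critical value on 298 df is 1.968, so the observed SMD must exceed 1.968/8.660 = 0.227 to enter the model. A continuous covariate with an observed SMD between 0.10 and 0.227 therefore fails the balance criterion and is still left out of the Cox model. The cut-off is 1.968/8.165 = 0.241 at 200:100 and 1.968/7.5 = 0.262 at 225:75.

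If the screen were run after successful matching, with at most 150 per group and every SMD below 0.10, then t would be below 0.10 × 8.660 = 0.87. No such covariate could be selected, and the rule would do nothing.

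**2. Chance that a truly imbalanced covariate is dropped** (1 − power, noncentral F):

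| True SMD | 150:150 | 200:100 | 225:75 | 102:103 (N = 205) |
|---|---|---|---|---|
| 0.10 | 86% | 87% | 88% | 89% |
| 0.15 | 75% | 77% | 80% | 81% |
| 0.20 | 59% | 63% | 68% | 70% |
| 0.25 | 42% | 47% | 54% | 57% |
| 0.30 | 26% | 32% | 39% | 43% |
| 0.40 | 7% | 10% | 15% | 19% |
| 50% point | 0.227 | 0.241 | 0.262 | 0.275 |

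A binary covariate at 40% versus 30% (SMD 0.21) is dropped 56% of the time at 150:150.

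**3. Bias from wholly omitting one confounder**, approximately exp(−SMD × ln HR per SD). At SMD 0.20 this is a hazard ratio of 0.95, 0.92 or 0.87 for a covariate with HR 1.3, 1.5 or 2.0 per SD.

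**4. Simulated trials with no device effect**, 150:150, independent confounders all favouring the device. False benefit means HR below 1 with two-sided p < 0.05 (nominal 2.5%). Rows 1 to 6 use 1,000 trials each and a 30% six-month risk at the control-group mean. The last row has about 105 events and repeat runs of 500 to 1,000 trials.

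| Confounders (SMD; HR per SD) | Unadjusted | ANOVA-screened | All prespecified |
|---|---|---|---|
| 1 (0.20; 1.3) | 0.95, 4.7% | 0.98, 2.9% | 1.00, 2.3% |
| 1 (0.20; 1.5) | 0.93, 5.5% | 0.98, 2.7% | 1.01, 2.3% |
| 3 (0.20; 1.3) | 0.87, 11.5% | 0.95, 4.6% | 1.01, 2.2% |
| 5 (0.20; 1.3) | 0.78, 20.6% | 0.92, 5.2% | 1.00, 1.9% |
| 3 (0.30; 1.3) | 0.80, 16.4% | 0.97, 3.0% | 1.00, 2.1% |
| 3 (0.40; 1.3) | 0.73, 29.2% | 0.98, 2.6% | 0.99, 2.4% |
| 6 (0.18; 1.3) | 0.77, 24.5–27% | 0.89–0.90, 6.0–7.8% | 1.00, 1.5–2.7% |

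The simulation standard error around 2.5% with 1,000 trials is √(0.025 × 0.975/1000) = 0.5 percentage points. Rates of 2.6 to 3.0% are therefore indistinguishable from nominal; those of 4.6% and above are not.

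**5. The planned matching.** In the six-confounder scenario, 1:1 nearest-neighbour propensity score matching on the full list gave HR 1.00 with 2.0% false benefit (500 trials). The caliper of 0.2 SD is an assumption; the article states none.

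**The case against.** The best defence is that the ANOVA sentence does not stand alone. Propensity score matching on a named list, which does not depend on the screen, follows directly, and in the worst scenario above it removed the bias. A reader might infer that the plan as written will produce a spurious device benefit. The documents do not support that. They give no imbalances, covariate strengths or event risk; the direction is only made plausible by the Limitations section; and the bias arises only if the screened model in the unmatched sample is the headline result.

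A reader might also infer that real confounders in general are lost more often than not. That holds only below an SMD of about 0.23 at 150:150. At 0.30 the loss is 26% and at 0.40 it is 7%. In every scenario run, the screen also removed at least about half of the unadjusted bias.

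Three smaller points stand for the defence. With two groups, ANOVA on a yes/no variable is close to a chi-square test, so its use for sex or diabetes is inelegant rather than damaging. The SMD criterion is attached to the propensity score step and the screen to the Cox model, so the two are inconsistent standards rather than a formal contradiction. An unadjusted log-rank test beside adjusted analyses is ordinary practice, provided the conclusion does not rest on it.

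What the defence does not answer is which analysis counts. Matching protects the primary hazard ratio only if that ratio comes from the matched analysis, and the section leaves this open.

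**Conclusion.** The point holds in a limited form. The covariate rule is stated in the plan, is unsound in principle, and at the planned size leaves out imbalances of 0.10 to about 0.23 SD more often than not, although the plan's own criterion calls these inadequate balance. If the screened Cox model is the headline result, the residual confounding in the scenarios run corresponds to a hazard ratio of about 0.89 to 0.98 under no effect. That is a spurious reduction of 2 to 11%, against a target of 20%. False benefit is about 3 to 8% instead of 2.5%. It is negligible with one confounder or with large imbalances, and largest when several moderate ones point the same way.

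These sizes rest on an assumed equal split and on assumed independent confounders that all favour the device. They show what the rule can do and do not predict this trial's result. The planned matching would largely remove the bias, so the defect lies in the selection rule together with the unnamed source of the primary hazard ratio.

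**What to change.** In Primary endpoint analysis:

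- Delete the ANOVA selection sentence.
- Prespecify the Cox covariates from the baseline list already named for the propensity score, with no selection by p-value. If events are few, limit them to the strongest prognostic ones, chosen before outcome data are seen. The list has about 15 entries even with electrolytes and LV volumes counted once each; at an assumed 105 events that is 105/15 = 7 events per entry, and fewer once categories are split.
- Name one adjusted analysis as the source of the primary hazard ratio, for example the propensity-matched Cox model already planned, and call the others sensitivity analyses.
- Label the unadjusted Kaplan–Meier and log-rank comparison descriptive.

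The cost is a few sentences and a slightly wider confidence interval from the extra covariates. No new data are needed.

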Optimized heart failure therapy for at least 1 month prior to enrolment	Terminal illness with limited life expectancy (e.g., metastatic cancer, end-stage lung disease)
Any LVEF phenotype (HFrEF, HFmrEF, HFpEF)	Pregnancy
≥1 hospitalization or outpatient visit with IV therapy for CHF in last 12 months	Dermatological conditions or allergies preventing prolonged use of the wearable device
Ability to provide informed consent or availability of a legally authorized representative	Cognitive or psychiatric disorders impairing adherence to study procedures

CHF, chronic heart failure; eGFR, estimated Glomerular Filtration Rate; HFmrEF, Heart Failure with mildly reduced Ejection Fraction; HFpEF: Heart Failure with preserved Ejection Fraction; HFrEF, Heart Failure with reduced Ejection Fraction; IV, intravenous; LVEF, left ventricular ejection fraction; NYHA, New York Heart Association; VAD, ventricular assist device.

All clinical, instrumental, and biochemical data will be recorded in anonymized case report forms and stored in a secure digital database. Biospecimens (blood and urine) will be collected and retained for secondary biomarker analysis. The study protocol adheres to the Declaration of Helsinki and Good Clinical Practice guidelines, and it was approved by the regional ethics committee (Comitato Etico Campania 2; Approval No. 185867). The trial is registered at ClinicalTrials.gov with the identifier NCT06909682.

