### Groups and interventions

2.2

Participants will be allocated to one of two non-randomized, parallel groups based on their acceptance to use the wearable device:
Intervention Group – AI-Based Remote Monitoring: Patients in this group will wear wearable devices continuously over a six-month period. The wearable device collects multimodal biometric data, including SpO₂, HRV, EDA, respiratory rate, skin temperature, pulse rate, and sleep metrics (actigraphy). These data are automatically transmitted to the SMART-CARE platform, where advanced AI algorithms analyse trends and detect early signs of clinical deterioration. In case of abnormal findings, the system generates alerts for the clinical team, which may initiate teleconsultations, therapy adjustments, or in-person evaluations to prevent acute decompensation.Control Group – Standard Clinical Follow-Up: Participants in the control group will receive standard CHF management in accordance with current European Society of Cardiology (ESC) guidelines. This includes outpatient visits every three months, ECG and echocardiographic assessments, and laboratory evaluations. No remote monitoring will be applied in this group. Clinical decisions, including medication adjustments, will be based on periodic clinical evaluations and patient-reported symptoms.

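### Baseline heart-failure therapy is not named among the propensity-score or stratification variables, so a residual imbalance between self-selected arms could be credited in part to the device

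*Protocol article*

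**What the plan says.** Section 2.2 sets out how patients reach their arm: "Participants will be allocated to one of two non-randomized, parallel groups based on their acceptance to use the wearable device". There is no randomisation, and sections 2.1 and 2.6.1 rely on statistical adjustment to deal with selection.

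The adjustment has four parts:

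- **Propensity score (2.6.1).** "The propensity score will be estimated using baseline variables including age, sex, LVEF phenotype, NYHA class, major comorbidities", with five comorbidity groups in brackets, then "prior HF hospitalizations, baseline biomarkers (BNP/NT-proBNP, renal function, electrolytes), and key echocardiographic indices (LVEF, LV volumes". Matching is 1:1 nearest neighbour without replacement.
- **Balance check (2.6.1).** "Covariate balance between groups will be evaluated using standardized mean differences (SMD), with values <0.10 indicating adequate balance".
- **Cox model (2.6.1).** "The model will be adjusted for all statistically significant covariates identified through ANOVA between the two groups". The variables to be screened are not listed.
- **Stratification (2.1).** "stratified analyses by age, sex, New York Heart Association class - NYHA, Left Ventricular Ejection Fraction - LVEF phenotype, and comorbidities".

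The one statement on background treatment is an entry criterion in Table 1, repeated in the text of section 2.1: "Optimized heart failure therapy for at least 1 month prior to enrolment". It names no drug classes or doses and applies to all three ejection-fraction phenotypes.

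**The concern.** In a cohort where patients pick their own arm, the primary hazard ratio is only as credible as the set of confounders that is adjusted for. The listed score is detailed, down to electrolytes and left-ventricular volumes, yet it does not name what the patient is being treated with.

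The article itself treats therapy as something that moves the outcome. The Introduction credits drug and device therapies with advances in management and presents timely therapeutic adjustment, diuretics included, as part of how monitoring may reduce admissions. Section 2.2 makes therapy adjustment one of the responses to an alert. If changing therapy is expected to change admissions, therapy at baseline is a plausible confounder whenever it also differs between those who accept the device and those who decline it.

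If the list is followed as written, a difference in background treatment that remains after matching would enter the primary hazard ratio. A balance table limited to the listed variables would not show it.

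**Working it through.** The documents give no figure for this point that could be reproduced. The check is a reading of every adjustment statement, followed by an illustration of size.

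**1. Where therapy could enter the analysis**

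| Route | Is baseline therapy named? |
|---|---|
| Propensity score, 2.6.1 | No, though the list is introduced as open |
| Stratified analyses, 2.1 | No |
| Cox covariates chosen by ANOVA, 2.6.1 | Candidate variables not listed |
| SMD balance check, 2.6.1 | Covariates not listed |
| Eligibility, 2.1 and Table 1 | Yes, as optimized for at least one month, regimen unspecified |

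**2. What the significance screen would catch**

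Assumption: 300 patients split 150 and 150. The article fixes no split because patients choose. For a binary therapy indicator with prevalence p1 (device) and p0 (control), two-sided alpha 0.05:

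- SMD = (p1 − p0) / √{[p1(1−p1) + p0(1−p0)]/2}
- Power = Φ{[(p1 − p0) − 1.96·SE0] / SE1}, where SE0 uses the pooled proportion and SE1 the separate ones

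For 60% versus 50%:

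- SMD = 0.10/√0.245 = 0.20, twice the article's own 0.10 limit.
- SE0 = √(2 × 0.55 × 0.45/150) = 0.0574 and SE1 = √(0.49/150) = 0.0572.
- Power = Φ[(0.10 − 0.1126)/0.0572] = Φ(−0.22) = 0.41.

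The same calculation gives:

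| Device vs control on therapy | Chance of being flagged |
|---|---|
| 60% vs 50% | 41% |
| 65% vs 50% | 75% |
| 60% vs 40% | 94% |
| 70% vs 50% | 95% |
| 70% vs 40% | over 99% |

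These are the chances *if* therapy is among the variables screened. If it is not, they are zero.

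**3. What an imbalance would do to the hazard ratio**

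Assumptions, none of them from the documents: the device has no effect, the therapy has a hazard ratio HR of 0.6 to 0.8 for admission, and the prevalence gap is what remains after the listed covariates. The standard approximation for one unadjusted binary confounder is

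apparent device hazard ratio = [p1·HR + (1−p1)] / [p0·HR + (1−p0)]

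| Device vs control on therapy | HR 0.6 | HR 0.7 | HR 0.8 |
|---|---|---|---|
| 60% vs 50% | 0.76/0.80 = 0.950 | 0.82/0.85 = 0.965 | 0.88/0.90 = 0.978 |
| 70% vs 40% | 0.72/0.84 = 0.857 | 0.79/0.88 = 0.898 | 0.86/0.92 = 0.935 |

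The reference is section 2.6.3: "The estimation assumes a 20% relative reduction in the rate of hospital admissions". The first row is a spurious reduction of 2% to 5%, about one-tenth to one-quarter of that 20%. The second row is 6.5% to 14%, about one-third to seven-tenths.

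**4. The opposite direction**

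If the control arm is the better-treated one, the ratios invert. For 50% (device) versus 60% (control), the apparent hazard ratio is 0.80/0.76 = 1.05 at HR 0.6 and 0.90/0.88 = 1.02 at HR 0.8.

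**5. What the balance rule would achieve if therapy were in it**

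At 55% versus 50%, SMD = 0.05/√0.24875 = 0.10, right at the limit. The apparent hazard ratio there is 0.78/0.80 = 0.975 at HR 0.6 and 0.89/0.90 = 0.989 at HR 0.8. Under these assumptions, applying the existing rule to such an indicator would hold the distortion to about 1% to 2.5%.

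**The case against.** The strongest reply is that this is an omission from an illustrative list. The score variables are introduced with the word *including*, the text is a condensed journal article, and nothing in it excludes therapy. That is formally right, so the article cannot be said to rule therapy out. But it does set out its covariates in detail, and an open list does not commit anyone to adding this one.

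Second, the ANOVA-selected Cox covariates are a further route. If therapy is screened, the large gaps (60% versus 40%, 70% versus 40%) would be flagged 94% of the time or more, and the imbalances likely to slip through are those that distort the hazard ratio by only 2% to 5%. This stands, and it means the 70% versus 40% row matters mainly if therapy is not screened. The article does not say whether it is.

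Third, both arms must be stable on optimized therapy, and matching uses phenotype, NYHA class, biomarkers, renal function and atrial fibrillation, all plausibly related to what a patient is prescribed. This narrows the residual gap. It does not close it, because patients alike on those variables can still differ in regimen.

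A reader might also infer three stronger things that the documents do not support:

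- *That the bias favours the device.* Volunteers may be better treated and more adherent, but sicker and more intensively treated patients might equally accept monitoring. The article is silent on this.
- *That a double-digit bias is to be expected.* The therapy hazard ratios and residual gaps are assumed, and no gap of 20 to 30 points after matching is evidenced.
- *That the biomarker and echocardiographic endpoints are biased by the same list.* For continuous variables, section 2.6.2 names paired or repeated-measures tests, and it uses propensity techniques only when appropriate, in the context of comparing phenotypes. The link to the primary endpoint's score is not shown.

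**Conclusion.** The point holds in a limited form. The arms are self-selected, and neither the itemised propensity-score list nor the stratification list names baseline heart-failure therapy. Neither the entry criterion nor the unspecified significance screen secures balance on it. A residual imbalance *could* be credited *in part* to the device, or could hide part of a real effect.

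The size is illustrative. With a null device and therapy hazard ratios of 0.6 to 0.8 unexplained by the listed covariates, the apparent hazard ratio is 0.95 to 0.98 for a moderate imbalance that the screen would usually miss. It is 0.86 to 0.94 for a large one that escapes adjustment altogether. The documents give neither the prevalence of any therapy nor its effect on admissions, so the actual bias cannot be estimated from them.

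**What to change.** In section 2.6.1, name baseline heart-failure therapy (use of each main disease-modifying drug class, and loop-diuretic use) as a prespecified propensity-score variable, and include it in the SMD balance table under the existing 0.10 limit. It should be in the score whether or not it differs significantly between arms.

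Use baseline values only. Therapy changes made after an alert are part of what the intervention does, and adjusting for them would remove part of the effect being estimated.

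The cost is small. Therapy has to be reviewed at entry to apply the eligibility criterion, so the information should be at hand and no clinical procedure changes. The price is a few more terms in an already long score and possibly slightly fewer matched pairs, out of at most 150 from 300 patients.
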